### Sample size calculation and power analysis

The sample size was calculated assuming that the proportion of smokers in the patient population is comparable with the smoking prevalence in the Finnish adult population, i.e. about 20%^36^. The other assumption was that with appropriate support before surgery, as many as half of the smokers could quit smoking. The sample (n=550) was calculated to observe 10% difference in postoperative complications between smokers and non-smokers, with 5% alpha error and 80% power, considering a 10% drop-out rate.

### Data analyses

To analyze the risk of primary outcome, i.e. the postoperative complications among smokers, non-smokers, and quitters, a logistic regression model will be used. The effectiveness of the smoking cessation intervention will be assessed using logistic regression analyses. Associations of smoking status and background variables with complications will be analyzed using log-linear models considering patients’ gender, age, and comorbidities.

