### Hypotheses

Smoking patients have more complications compared with non-smoking patients and patients continuing smoking despite smoking cessation intervention have more complications than initially smoking patients who are stopping smoking because of the intervention.Smoking cessation of patients with planned arthroplasties or heavy spine operations or other heavy operations, and of patients with low or moderate nicotine dependence, is successful more often than in other patients.

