## DISCUSSION

In studies concerning smoking and orthopedic surgery, the definition of smoker and/or smoking status has been diverse. For example, ex-smokers are classified as non-smokers; mostly, smoking status is based only on patients’ self-report without any biochemical verification. Bender et al.^35^ showed in their study of patients who had had surgery for long bone non-union that 23% of participants reporting to be former smokers and 6% of participants reporting to be non-smokers had serum cotinine values suggesting that they were active smokers. In this study, laboratory tests will be performed to biochemically verify participants’ smoking status to increase the evidence for the effect of smoking on the outcome of orthopedic surgery. Thus, some participants who report to be non-smokers could be classified as active smokers based on the laboratory tests.

Ehnert et al.^39^ showed that the rate of complications after joint arthroplasty of smokers exceeds that of non-smokers and increasing number of cigarettes smoked raises the rate of complications. Also, they showed that bone formation and inflammatory response markers of smokers are lower than those of non-smokers. However, the aim of this study is to gather evidence on the effects of biochemically confirmed smoking and smoking cessation on the outcome of defined, but otherwise unselected orthopedic and hand surgery operations and on feasibility and effects of a preoperative smoking cessation intervention. The intervention will be carried out in real-life settings, so all smokers will receive the smoking cessation intervention following a standard protocol. Randomization to smoking cessation intervention (yes or no) among active smokers would be an unethical study design. Further aims are to assess the factors affecting the feasibility and outcome of the intervention and its effects on costly complications which are more likely to occur among smokers than non-smokers. This valuable information could be used in future to support orthopedic or hand surgery patients in smoking cessation.

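### The covariates named for the complication analyses leave out operation type and nicotine dependence, the two factors the plan expects to predict quitting, so the quitter versus continuing-smoker comparison is open to confounding

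*Protocol article*

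**What the plan says.** The Data analyses section of the protocol article has three sentences.

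- Primary outcome: "To analyze the risk of primary outcome, i.e. the postoperative complications among smokers, non-smokers, and quitters, a logistic regression model will be used". No covariate is named.
- Intervention: "The effectiveness of the smoking cessation intervention will be assessed using logistic regression analyses". No covariate is named.
- Smoking status and background variables in relation to complications: "will be analyzed using log-linear models considering patients’ gender, age, and comorbidities".

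The Hypotheses section makes two statements that bear on this. First, it predicts more complications in those who keep smoking than in those who stop because of the intervention. Second, it says who will stop: "Smoking cessation of patients with planned arthroplasties or heavy spine operations or other heavy operations", together with cessation of patients whose nicotine dependence is low or moderate, "is successful more often than in other patients".

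The Discussion states that every smoker receives the intervention and that randomisation was ruled out. It describes the case mix as "defined, but otherwise unselected orthopedic and hand surgery operations".

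Both missing variables are collected. Planned surgery goes on the study form (Data collection), operation details come from the infection register (Data from operation and definition of complications), and the Fagerström test is given to smokers (Intervention). Type of surgery enters the analysis only in Primary and secondary outcomes, as a stratifier of the secondary outcomes.

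**The concern.** Quitters and continuing smokers form themselves into groups, so covariate control is the main protection for this comparison. A variable confounds it if it is related both to quitting and to complications. The plan supplies the first half of that condition for two variables, as its own hypothesis, and then names a covariate list that contains neither.

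The second half is plausible for both. The outcome counts prolonged stay and any additional test, treatment or visit, and the operations run from hand surgery to arthroplasty and spine surgery. For dependence, the Discussion cites a study of joint arthroplasty in which complications rose with the number of cigarettes smoked.

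The first aim and the first hypothesis both rest in part on this contrast. If the second hypothesis is right, the crude answer to the quitter part of the first may reflect who quit rather than what quitting did.

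**Working it through.** **Group sizes.** The plan gives no figure on this point to reproduce. Its sample size section supplies 550 recruited, 10% drop-out, about 20% smokers, and up to half of them quitting.

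- Analysed: 550 × 0.90 = 495.
- Smokers: 495 × 0.20 = 99.
- Quitters and continuing smokers: 99 × 0.50 = 49.5 each, about 50.

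**Bias from operation type alone.** The documents give no complication or quit rates by operation, so all the rates below are assumptions. Let half the smokers have a heavy operation, with quit rates a (heavy) and b (other), where a + b = 1 so that half quit overall. The heavy share is then a among quitters and b among continuing smokers. Let the complication risks be H (heavy) and L (other), and let quitting have no effect.

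- Crude risk in quitters = aH + bL.
- Crude risk in continuing smokers = bH + aL.
- Spurious difference = (a − b)(H − L).

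Stronger example, a/b = 65/35% and H/L = 30/10%:

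- Quitters: 0.65 × 0.30 + 0.35 × 0.10 = 0.23.
- Continuing smokers: 0.35 × 0.30 + 0.65 × 0.10 = 0.17.
- Difference 6 points against quitting; odds ratio (0.23/0.77)/(0.17/0.83) = 1.46.

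Milder example, 60/40% and 30/15%:

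- Quitters: 0.60 × 0.30 + 0.40 × 0.15 = 0.24.
- Continuing smokers: 0.40 × 0.30 + 0.60 × 0.15 = 0.21.
- Difference 3 points; odds ratio 1.19.

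Wider range. In the last column the risks H and L apply to continuing smokers, and the true odds ratio within each operation type is 0.50.

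| Quit rates a/b | Risks H/L | Quitters | Continuing | Difference | Crude OR, no effect | Crude OR, true 0.50 |
|---|---|---|---|---|---|---|
| 60/40% | 30/20% | 26% | 24% | 2 | 1.11 | 0.56 |
| 60/40% | 30/15% | 24% | 21% | 3 | 1.19 | 0.60 |
| 60/40% | 40/20% | 32% | 28% | 4 | 1.21 | 0.62 |
| 65/35% | 30/10% | 23% | 17% | 6 | 1.46 | 0.75 |
| 70/30% | 30/20% | 27% | 23% | 4 | 1.24 | 0.62 |
| 70/30% | 30/15% | 25.5% | 19.5% | 6 | 1.41 | 0.72 |
| 70/30% | 40/20% | 34% | 26% | 8 | 1.47 | 0.75 |

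If quit rates are equal (a = b) or risks are equal (H = L), the spurious difference is zero.

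**Effect on a real benefit.** Take 65/35% again, with risks of 35/15% in continuing smokers and a true 10-point benefit in each stratum, so 25/5% in quitters.

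- Quitters: 0.65 × 0.25 + 0.35 × 0.05 = 0.18.
- Continuing smokers: 0.35 × 0.35 + 0.65 × 0.15 = 0.22.
- The 10-point benefit appears as 4 points.

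**Bias from nicotine dependence.** The same product formula applies with the sign reversed. If highly dependent smokers quit less and have more complications, quitters look better than they should. A 30-point gap in the share of highly dependent smokers combined with a 20-point gap in risk would give 0.30 × 0.20 = 6 points in favour of quitting, which is the size of the stronger example above. Nothing in the documents says which of the two is larger.

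**The case against.** The best defence is that this is a condensed article. It names a model class and does not describe the model as crude, and a full covariate list is commonly left to an analysis plan. That stands, and a reader who infers that the primary model is unadjusted goes further than the text. What remains is narrower: the article does state a set of covariates, and that set omits the factors its own hypothesis ties to quitting.

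A second defence is that surgery type was considered. Secondary outcomes are stratified by it, and secondary aim (a) compares types of complication across patient subgroups. The log-linear models also take in background variables, which in Data collection cover medication, socio-economic status, physical activity and alcohol as well as chronic diseases. This is true, but none of it places operation type in the primary analysis, and operation details are recorded separately from the background questionnaire.

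Three other strong readings are tempting and are not supported:

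- That the comparison is confounded. This also needs operation type or dependence to affect complication risk. It is plausible, but the documents give no rates, and the broad outcome might vary little with the operation.
- That the bias must run against quitting. That follows for operation type alone, if heavy operations are riskier. Dependence could offset or reverse it.
- That there are two competing primary answers. The primary outcome is tied to logistic regression. The log-linear models fit secondary aim (b), on other explanatory factors, and the article does not call them primary.

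Finally, the argument concerns quitters against continuing smokers. The sample size was set for smokers against non-smokers, and the hypothesis about who quits does not directly touch that contrast.

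**Conclusion.** The point holds in a limited form. The covariates named in the article omit operation type and nicotine dependence, both of which the plan expects to predict quitting, so a non-randomised comparison that is part of the first hypothesis is open to confounding.

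For operation type alone, and only if heavier operations carry more complications, the bias is against a benefit of quitting. It is 3 to 6 points in the two worked examples and 2 to 8 points over the wider range, with crude odds ratios of 1.11 to 1.47 when quitting does nothing. Against the 10-point difference used for planning, that could be material. The size rests wholly on assumed rates, and the net direction is unknown once dependence is considered. This should be settled before the analysis. It does not affect the sample size of 550, and it does not by itself undermine the smoker versus non-smoker comparison.

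**What to change.** In Data analyses, or in the analysis plan with a pointer from the article:

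1. Name one adjusted logistic model of any complication as the primary analysis, with smoking group, operation type or size in a few categories (study form or infection register), age, gender and comorbidity.
2. For quitters against continuing smokers, add the Fagerström score. It is measured only in smokers, so this contrast needs a model restricted to initial smokers.
3. State that the log-linear models are secondary.

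Reporting an adjusted risk difference beside the odds ratio would match the 10-point planning difference, but that is a preference.

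The cost is wording and a few degrees of freedom; no new data are needed. The constraint is the smoker-only model. With 99 smokers and, say, 20% to 30% having a complication (assumed), there would be about 20 to 30 events (99 × 0.20 = 19.8; 99 × 0.30 = 29.7). The covariates there should be few, or be combined in a propensity score. Adjustment will not make this contrast precise: with about 50 per group, power for a 10-point difference is only about 17% to 28%, for a lower risk between 40% and 10%. It should be reported as an estimate with its interval.

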### Aims

This article describes the protocol of our study which aims to determine: 1) the effects of smoking and smoking cessation intervention on the incidence of complications after orthopedic surgery; 2) the feasibility of preoperative smoking cessation intervention and its effect on reducing smoking; and 3) which factors predict success in smoking cessation. The secondary aims of the study are: a) to compare the incidence of different types of complications in the whole study population and in different subgroups of orthopedic and hand surgery patients who are smokers, non-smokers or quitters who stopped smoking during the preoperative intervention; and b) to determine which other factors in addition to smoking, such as chronic diseases and medication, explain the incidence of complications.

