### Strengths and limitations

The strengths include that the study population will be recruited from a central hospital serving the whole population of a catchment area. Further, laboratory tests will be taken to biochemically verify participants’ smoking status to increase accuracy of smoking status assessment among the patients. A potential limitation is that the smoking cessation interventions will be carried out during the clinical work in the orthopedic and hand surgery outpatient departments and surgical wards at the non-teaching central hospital. Further, because of previous evidence of effectiveness of smoking cessation intervention, randomized trial design was not feasible. Finally, there will be probably overrepresentation of non-smoking patients for the study due to the requirement of filling a long questionnaire, complying with extra laboratory tests to be taken twice, and answering follow-up phone calls three times presumed during the study.

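### The effect of the cessation intervention cannot be estimated: every smoker receives it and no smoker comparator is described, so the effectiveness analysis and the matching parts of aims 1 and 2 and hypothesis 1 need rewording

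*Protocol article*

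**What the plan says.** Aim 1 covers "the effects of smoking and smoking cessation intervention on the incidence of complications after orthopedic surgery", and aim 2 covers "the feasibility of preoperative smoking cessation intervention and its effect on reducing smoking" (Aims). Hypothesis 1 sets continuing smokers against "initially smoking patients who are stopping smoking because of the intervention" (Hypotheses). The Data analyses section uses logistic regression to compare complications among smokers, non-smokers and quitters, and then adds: "The effectiveness of the smoking cessation intervention will be assessed using logistic regression analyses". That sentence names neither an outcome nor a comparator.

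On who is treated, the Discussion says "so all smokers will receive the smoking cessation intervention following a standard protocol" and gives the reason: "Randomization to smoking cessation intervention (yes or no) among active smokers would be an unethical study design". Strengths and limitations repeats that a "randomized trial design was not feasible". The outcomes section treats successful cessation as a feasibility outcome. The sample size section powers smokers against non-smokers and assumes that up to half of the smokers might quit.

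**The concern.** An effect of an intervention is a contrast between having it and not having it. Here no smoker is without it, and the article names no outside group to stand in. Three places nevertheless promise such an effect: on complications (aim 1), on smoking (aim 2) and on both through the hypothesis that patients stop because of it. The effectiveness sentence then assigns a method to a quantity that the design cannot supply.

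The likely substitute is the comparison of quitters with continuing smokers. Those groups are formed by what patients did after the intervention, not by whether they received it. Hypothesis 2 itself expects quitting to be commoner with low or moderate nicotine dependence and in patients facing arthroplasty, spine or other heavy operations. Type of surgery plausibly bears on complications directly. If this odds ratio were published under the label of effectiveness, readers would take a self-selected association for a causal effect of the programme.

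**Working it through.** **1. Is there an intervention coefficient?** Inputs: 550 patients and 20% smokers (Recruitment; Sample size calculation), so 550 × 0.20 = 110 smokers and 440 non-smokers. All smokers are treated (Discussion). The Intervention section describes it for smokers only.

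- Whole cohort, columns (intercept, smoker, intervention): 440 rows of (1, 0, 0) and 110 rows of (1, 1, 1). The last two columns are identical, so the rank is 2 for 3 columns.
- Smokers only, columns (intercept, intervention): 110 rows of (1, 1). The rank is 1 for 2 columns.

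The coefficient is fully aliased with smoking status in the first case and with the intercept in the second. More patients add more copies of the same rows, so sample size does not help. This holds whether the outcome is complications or quitting.

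**2. Does variation in content rescue it?** Nicotine replacement or prescription medication depends on the level of nicotine dependence (Intervention). That would allow forms of the intervention to be compared, confounded by dependence. It does not create a smoker without the intervention.

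**3. What can be estimated?**

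| Stated target | Contrast needed | Available? |
|---|---|---|
| Smoking and complications (aim 1) | Smokers vs non-smokers | Yes, as an association |
| Intervention and complications (aim 1) | Smokers with vs without intervention | No |
| Feasibility (aim 2) | Quit proportion in treated smokers | Yes |
| Intervention and reduction of smoking (aim 2) | Quitting with vs without intervention | No; only an uncontrolled before-after description |
| Predictors of quitting (aim 3) | Within treated smokers | Yes |
| Stopping because of the intervention (hypothesis 1) | Separating it from stopping anyway | No |

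**4. How large is the remaining contrast?** With 10% drop-out, 550 × 0.9 × 0.2 = 99 smokers. If half quit, that is 49.5 against 49.5. Two-sided 5% power from the normal approximation is

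Φ{[d − 1.96·√(2p̄(1−p̄)/n)] / √([p₁(1−p₁)+p₂(1−p₂)]/n)}, where d = p₁ − p₂, p̄ is the mean of p₁ and p₂, and n = 49.5.

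Worked for 38% vs 20%: p̄ = 0.29; null standard error √(0.4118/49.5) = 0.0912, times 1.96 = 0.1788; alternative standard error √(0.3956/49.5) = 0.0894; (0.18 − 0.1788)/0.0894 ≈ 0.01, so power is about 51%.

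| Complication rates | Source | Power |
|---|---|---|
| 38% vs 20% | Introduction | 51% |
| 41% vs 21% | Introduction | 58% |
| 52% vs 18% | Introduction | 96% |
| 20% vs 10% | Assumed | 28% |

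The Introduction's rates come from intervention and control groups, not from quitters and continuing smokers, so they only indicate scale.

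**5. The stated 550.** It is set for smokers against non-smokers. No baseline complication rate is given, so it cannot be reproduced uniquely. At 1:4, two-sided, with 10% drop-out, an assumed 8% vs 18% gives 562 and 10% vs 20% gives 639. The present point does not depend on it.

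**The case against.** The best defence is that the effectiveness sentence names no intervention term. It can be read as a logistic model of quitting among treated smokers, with effectiveness as a loose label. The article is a condensation, and the exact model may stand in a fuller document. The abstract speaks of smoking and smoking cessation together with feasibility, which is close to what the data can support. The absence of randomisation is openly stated and justified.

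Much of this stands, and it limits the point. The absence of randomisation is not the error. The article also does not say which contrast will be reported as effectiveness, so one can say only that the quitter comparison could be misused, not that it will be. But a model of quitting among treated smokers yields predictors of quitting, which is already aim 3; it does not yield an effect of the intervention. This is not a detail left to another document either. Treatment of all smokers is stated, and no choice of model creates a comparator.

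Two further readings should not be pressed:

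- A reader might infer that aims 1 and 2 fail altogether. They do not: the smoking half of aim 1 and the feasibility half of aim 2 are untouched.
- A reader might infer that smokers detected only by laboratory test miss the intervention and distort the quit proportion. The tests belong to the preoperative assessment, and the intervention is also given at the preoperative visit, so the article does not show that they miss it.

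**Conclusion.** The concern holds in a bounded form. The effect of the intervention, on complications or on quitting, is not identifiable at any sample size. The effectiveness sentence, the intervention-effect parts of aims 1 and 2, and the causal clause of hypothesis 1 therefore have no estimable target. The powered comparison of smokers with non-smokers is not affected by this point.

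The conclusion assumes that all smokers are treated, as stated, and that no external or historical smoker group is defined in a document not shown. The figure of about 50 against 50 further assumes exactly 20% smokers, half quitting and equal drop-out; the article aims for at least 20%, so the number could be larger. The power figures describe the substitute contrast. They do not measure the identifiability problem, and neither would the precision of a quit proportion.

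**What to change.** Replace the effectiveness sentence under Data analyses with three items:

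- (a) the quit proportion with a 95% confidence interval among smokers offered the intervention;
- (b) logistic regression for predictors of quitting;
- (c) complications in quitters against continuing smokers, adjusted for dependence score and type of surgery in addition to the gender, age and comorbidities already planned, and reported as an association with cessation.

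Reword aims 1 and 2 and hypothesis 1 to speak of quitting after being offered the intervention, and align the Discussion's mention of its effects on complications.

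The dependence test and the planned surgery are already recorded, so no new data are needed. The cost is a weaker claim. Item (c) will also be imprecise: at the mean of the cited 38% and 20%, 99 × 0.29 ≈ 29 events would have to support quit status and five adjustment variables, so surgery type should be grouped coarsely and the interval shown without a claim of effect.
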